### Randomization and allocation

2.8.

All participants will be stratified by BMI using the World Health Organization (WHO) cutoff. Overweight (BMI of 25–30 kg/m^2^) and obese (BMI of >30 kg/m^2^) adults will be randomly distributed into blocks of 4, 6, and 8. Within these blocks, each participant will be randomly allocated to the intervention group (MyGeneMyDiet^®^) or control (standard weight management recommendation) using a Random Allocation Software.^1^ Two research staff will perform the randomization.

During randomization, 62 identical (31 for each treatment) sequentially numbered, opaque sealed envelopes (SNOSE) will be prepared. The sequential numbering will be synchronized with the online registration and will be used to designate participant study numbers. The randomization allocation will be concealed from the participants and the rest of the researchers involved in the month 0 visit.

### Data collection methods

2.9.

Study outcomes will be assessed at five time points: baseline (month 0), and months 3, 6, 9, and 12. Table 2 provides an overview of data collection and outcome measures.

**Table 2 tab2:** MyGeneMyDiet^®^ study data collection and outcome measures.

Outcome measures	Active phase			Inactive phase	
	Baseline (Month 0)	Month 3	Month 6	Month 9	Month 12
Demographic information	X				
Anthropometry (weight, BMI, waist circumference, hip circumference, percent body fat)	X	X	X	X	X
Dietary intake (3-day food record)*	X	X	X	X	X
Blood chemistry analysis (glycated hemoglobin, lipid profile)	X	X	X	X	X
Physical activity level (IPAQ-SF)	X	X	X	X	X
Eating behavior (TFEQ R-18)	X	X	X	X	X
Motivation for weight loss (SP-Weight Loss)	X	X	X	X	X
Knowledge and perception of nutrigenomics	X		X		X

* Monthly 3-day food records are also collected from the participants, in addition to the food records collected on months 0, 3, 6, 9, and 12.

The research team will conduct the screening and subsequent data collection sessions at the Food and Nutrition Research Institute, Taguig City, Philippines. Pre-session visits will be conducted 2 weeks before the online nutrition counseling sessions.

#### Anthropometric measurements

2.9.1.

Body weight and body fat percentage will be determined using a body composition analyzer (Tanita-MC78U, Tanita Corporation, Japan). Height will be measured using a stadiometer (Seca 217, Seca, Germany) while waist and hip circumference will be obtained using a non-stretchable tape measure (Seca 203, Seca, Germany). Anthropometric measurements will be done twice following a standard procedure. A third measurement will be taken if the difference between the two measurements is greater than 0.3 kg for weight, 0.5 cm for height, and 0.5 cm for waist circumference. The average of all the readings will be taken as the final estimated value of the measurement. BMI will be derived by dividing the weight in kilograms by height in meters squared. The percent body fat (BF%) will be assessed according to the chart by Gallagher et al. (39).

#### Dietary intake

2.9.2.

On a monthly basis, participants will be asked to complete a three-day food diary to estimate their mean energy and macronutrient intake while enrolled in the trial. The food record will consist of two non-consecutive weekdays and one weekend. In total, the participants will accomplish 12 sets of food diaries during the trial.

Proper recording of food and beverage intake and estimating food portion sizes will be explained to the participants during the orientation session. The food diary must reflect all the food and beverages consumed by the participants within the specified periods, the description of each food items (type, variety, brand name), amounts, the time of the day the meal is taken, cooking method (e.g., boiled, fried, broiled), and the source of the food (e.g., home-cooked or takeaway). A food diary form (printed or in electronic form, depending on the participant’s preference) will be distributed during the pre-session visits or approximately 2 weeks before the online follow-up sessions.

Checking and verification to ensure the completeness and correctness of the recorded intake will be done by the nutritionists of the research team, 2 weeks before the online nutrition counseling session. This will provide sufficient time for the nutritionists to analyze the dietary intake of the participants. Energy and macronutrients will be computed using the Philippine Food Composition Tables (FCT). Other foreign FCTs will be used for the items not found in the local FCT.

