### Study design

2.1.

The MyGeneMyDiet^®^ study is a parallel-group, single-blind, randomized controlled trial (Figure 1). Sixty-two overweight or obese adults will be recruited through waves of study enrollment. The 12-month trial will entail an “active” phase (first 6 months), followed by an “inactive” phase from months 7–12. During months 1–6, all participants will receive three sessions of nutrition counseling, including general health and information presented in nutrition modules designed for the study. A simulation of a “free-living state” will be applied to the participants during months 7–12. During this period, a follow-up data collection on month 9 and the nutrition counseling session at the end of the study on month 12 will be initiated. The inactive phase will determine whether the participants continue to adhere to the dietary and lifestyle recommendations given to them during the active phase.

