### Outcomes

2.7.

The primary outcomes will be the difference in weight, BMI, waist circumference, and body fat percentage between the arms after both the active and inactive phases. Secondary outcomes will include improvement in dietary intake, eating behavior, physical activity levels, glycated hemoglobin, and blood lipid profile. In addition, stages and motivation for weight loss and the knowledge and perceptions in nutrigenomics and genetic testing will be evaluated.

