### Statistical analysis plan

2.10.

Outcome data will be reported following the Consolidated Standard Reporting Trials (CONSORT) guidelines (46). An intention-to-treat analysis will be employed.

The mean and standard deviation (SD) will be used to report continuous variables while percentages will be used for categorical variables. Estimates of the different sources of attrition bias will be conducted using two-way analysis of variance (ANOVA) models. Student *t*-test will be used to compare the differences in means between the intervention and the control group for the primary and secondary outcome measures. One-way ANOVA will be used if the comparison of multiple subclasses is warranted, with Dunn’s multiple comparisons *post-hoc* test. Linear mixed models will be used to determine changes from baseline among the different study outcomes, with participant number retained as random effect. A two-sided alpha of 0.05 will be used for hypothesis testing.

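### Diaries are collected monthly, but neither stated use gives an all-diary estimate of dietary intake for each phase, and the diary count does not match Table 2

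*Protocol article*

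**What the plan says.** Section 2.7 lists diet among the secondary outcomes: "Secondary outcomes will include improvement in dietary intake, eating behavior, physical activity levels". Section 2.9 fixes when outcomes are measured: "Study outcomes will be assessed at five time points: baseline (month 0), and months 3, 6, 9, and 12". Table 2 marks a 3-day food record at each of these visits, with months 3 and 6 under the active phase and months 9 and 12 under the inactive phase. Its footnote adds: "Monthly 3-day food records are also collected from the participants, in addition to the food records collected on months" 0, 3, 6, 9 and 12.

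Section 2.9.2 describes the monthly collection: "participants will be asked to complete a three-day food diary to estimate their mean energy and macronutrient intake while enrolled in the trial". On content it says "The food record will consist of two non-consecutive weekdays and one weekend", and on the total, "In total, the participants will accomplish 12 sets of food diaries during the trial".

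Section 2.1 gives the reason for the second half of the trial: "The inactive phase will determine whether the participants continue to adhere to the dietary and lifestyle recommendations given to them during the active phase".

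Section 2.10 names two analyses that bear on diet. A Student t-test "will be used to compare the differences in means between the intervention and the control group for the primary and secondary outcome measures", and linear mixed models with participant as a random effect are used for changes from baseline.

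**The concern.** Intake is the secondary outcome closest to the calorie and fat advice that separates the arms. The design asks a phase-specific question about it: is the advice followed in months 1-6, and does that last through months 7-12? Diaries are to be collected in every month of both phases, so an estimate per phase from all of them is available at no extra burden. The article describes two other uses: values at five visits, and a mean over enrolment.

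Each has a cost, and the costs differ. With visit values only, eight diaries (months 1, 2, 4, 5, 7, 8, 10 and 11) would not contribute, and each time point would rest on one 3-day record, which carries much day-to-day variation. With one mean over the whole trial, every diary contributes but a difference that fades after month 6 cannot be seen. A t-test also leaves the baseline diary unused as a covariate.

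The diary count matters for the same reason. If the 12 sets are months 1-12 and the total is taken at face value, it is unclear whether a month 0 diary exists, and change from baseline depends on it.

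**Working it through.** **Diary count.** The stated total is 12.
- Months 1 to 12, one each: 12. This reproduces the figure, but only if the month 0 record in Table 2 is not counted.
- Months 0 to 12, one each: 13. This is what Table 2 with its footnote gives if visit and monthly records coincide.
- Twelve monthly records on top of five visit records, taking the footnote literally: 12 + 5 = 17.

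**Precision: inputs.** Three days per record (2.9.2). Two post-baseline visit records per phase (Table 2). Six monthly diaries per phase (months 1-6 and 7-12). The document gives no variances for intake, so these are assumed: between-person CV (B) 15-25%, within-person day-to-day CV (W) 20-30%, independent days, and stable intake within a phase.

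**Formulas.** The variance of a person's mean over k records is V(k) = B² + W²/(3k). With the month 0 record as covariate, the residual variance is A(k) = V(k) − B⁴/V(1). The standard error (SE) of the arm difference is proportional to the square root of either, so the ratios do not depend on the number per arm.

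**Results at the two extremes of the assumed range:**

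| | B = 15, W = 30 | B = 25, W = 20 |
|---|---|---|
| V(1) | 225 + 300 = 525 | 625 + 133.3 = 758.3 |
| V(2) | 225 + 150 = 375 | 625 + 66.7 = 691.7 |
| V(6) | 225 + 50 = 275 | 625 + 22.2 = 647.2 |
| SE ratio, six v two | √(275/375) = 0.86 | √(647.2/691.7) = 0.97 |
| SE ratio, six v one | √(275/525) = 0.72 | √(647.2/758.3) = 0.92 |
| B⁴/V(1) | 50625/525 = 96.4 | 390625/758.3 = 515.1 |
| A(1), A(2), A(6) | 428.6, 278.6, 178.6 | 243.2, 176.6, 132.1 |
| Adjusted SE ratio, six v two | 0.80 | 0.865 |
| Adjusted SE ratio, six v one | 0.65 | 0.74 |

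Six diaries against the two visit records of a phase therefore lower the SE by about 3-14%, which is worth 691.7/647.2 = 1.07 to 375/275 = 1.36 times the sample. With both sides baseline-adjusted the reduction is about 14-20%. Against a single visit record the figures are 8-28%, and 26-35% with both adjusted.

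**Cross-check by another route.** Assume instead a correlation between records (ICC) of 0.3-0.7, equal for all pairs, and a relative variance of ICC + (1 − ICC)/k. Six against two then lowers the SE by 6-20%, and six against one by 13-36%, both unadjusted. The order of size is the same.

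**Phase contrast under a whole-trial mean.** Let f be the share of the active-phase arm difference that is kept in months 7-12. A mean over twelve monthly diaries shows (1 + f)/2 of the active-phase difference: 50% if f = 0, 75% if f = 0.5 and 100% if f = 1. One number cannot separate a smaller lasting difference from a larger one that faded.

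**The case against.** The strongest reply is that the article leaves the handling of the between-visit diaries open and does not mishandle them. A reader might infer that these diaries are discarded. Nothing in the text says so, and the mixed model in 2.10 could take every monthly record. A reader might also infer that one whole-trial mean will be compared between arms. The sentence in 2.9.2 allows this, but it can equally mean that each monthly diary yields a mean daily intake, repeated through enrolment. Both points stand.

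It would also be wrong to charge the plan with both costs together. The five-visit schedule has two post-baseline records in each labelled phase, so it preserves the contrast. The whole-trial mean loses no diaries. It follows that the fair comparator for a phase estimate is two visit records, not one, and the gain is then modest.

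A tempting illustration is a 150 kcal arm difference halved to 75 kcal by averaging over both phases. The document does not support this as an expected difference. Table 1 ties the 150 kcal reduction to the *UCP1* variant, and eligibility requires only one of three risk alleles, so not every intervention participant receives that advice.

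Finally, a phase average assumes fairly stable intake within the phase. If intake drifts, the average blurs the time course. Checking of diaries in 2.9.2 is also tied to the counseling sessions, so between-visit diaries may be less closely verified. These are reasons to keep the visit values alongside the phase estimates. They do not remove the need to say how the monthly diaries are used.

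**Conclusion.** The point holds as a worthwhile improvement to a secondary outcome. As written, neither the five-visit values nor a mean over enrolment gives an estimate of intake per phase from all diaries, although phase-specific adherence is a stated purpose of the design, and the t-test leaves the baseline diary unused. The gain over two visit records per phase is a 3-14% lower SE, or 14-20% with both adjusted for baseline. The larger figures (8-28% and 26-35%) apply only if arms are compared at a single visit. All rest on assumed variances and on stable intake within a phase. Loss of the phase contrast arises only under the whole-trial reading, which the text permits but does not state.

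The count is a plain inconsistency: 12 cannot cover both the month 0 and month 12 records of Table 2 and a diary in every month between. Nothing here touches the primary outcomes.

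**What to change.** - In 2.9.2 and 2.10, define the dietary comparison as the arm difference in mean daily energy and macronutrient intake for months 1-6 and for months 7-12, each estimated from all monthly diaries in that phase.
- Estimate both in the linear mixed model already planned, with arm-by-phase terms, participant as random effect and the month 0 diary as covariate.
- Keep the five-visit values as a sensitivity analysis and to show the time course.
- Reword the purpose sentence in 2.9.2 so that it is clear whether the mean is per diary, per phase or over the whole trial.
- Reconcile the total of 12 with Table 2 and its footnote: 13 if months 0-12 are each recorded once, 12 only if the baseline record is counted separately. State whether the monthly records include the visit records, and confirm that a month 0 diary is collected.

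The cost is a few sentences and a slightly larger model. No new data and no extra participant burden are needed. The one downside is reliance on between-visit diaries that may be less closely checked, which the sensitivity analysis addresses.

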#### Biochemical data

2.9.3.

Blood samples will be collected during the specified time points (months 0, 3, 6, 9, and 12). The participants will be asked to undergo 10–12 h of fasting before specimen collection. A phlebotomist will collect approximately 5 mL of blood for the analysis of glycated hemoglobin and lipid profile.

#### Physical activity

2.9.4.

The International Physical Activity Questionnaire – Short Form (IPAQ-SF) will be used to measure the level of physical activity of the participants. The short version has seven questions to assess the type and intensity of physical activity that individuals do as part of their daily lives and to estimate the total physical activity in metabolic equivalent (ME).

#### Eating behavior

2.9.5.

The Three-Factor Eating Behavior Questionnaire (TFEQ-R18) (40) will evaluate the eating behavior of the participants. The questionnaire will capture the current dietary practices and aspects of eating behavior such as cognitive restraint eating (conscious restriction of food intake), uncontrolled eating (tendency to eat more than usual due to loss of control over intake accompanied by subjective feeling of hunger), and emotional eating (inability to resist emotional cues).

#### Level of motivation to change

2.9.6.

The Stages (S-Weight) and Process (P-Weight) of Change for Weight Loss Questionnaire will be used to assess the participants’ motivation to lose weight. The S-Weight consists of five mutually exclusive items that will allocate the participants to one of the five stages of change: pre-contemplation, contemplation, preparation, action, and maintenance (41, 42). The P-Weight is a 34-item questionnaire that measures the four processes of change: emotional re-evaluation, weight management actions, environmental restructuring, and weight consequences evaluation (41–44).

#### Knowledge and perceptions on genetic testing and nutrigenomics

2.9.7.

Participants will be asked to complete a survey designed to assess awareness, perceptions, and self-efficacy toward genetic testing and nutrigenomics. Written permission from the main author of the questionnaire (45) was sought before using it for this study.

### Statistical analysis plan

2.10.

Outcome data will be reported following the Consolidated Standard Reporting Trials (CONSORT) guidelines (46). An intention-to-treat analysis will be employed.

The mean and standard deviation (SD) will be used to report continuous variables while percentages will be used for categorical variables. Estimates of the different sources of attrition bias will be conducted using two-way analysis of variance (ANOVA) models. Student *t*-test will be used to compare the differences in means between the intervention and the control group for the primary and secondary outcome measures. One-way ANOVA will be used if the comparison of multiple subclasses is warranted, with Dunn’s multiple comparisons *post-hoc* test. Linear mixed models will be used to determine changes from baseline among the different study outcomes, with participant number retained as random effect. A two-sided alpha of 0.05 will be used for hypothesis testing.

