### Sample size calculation

2.5.

To address the primary research question, at least 52 participants (*n* = 26 per group) are needed to detect a clinically meaningful difference of 5% weight loss after 6 months of intervention, assuming 80% power, an alpha of 5%, and a 0.25 SD in the main outcome variable (31). We aim to recruit 62 participants (*n* = 31 per group) to account for the potential dropout rate of 20%.

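### The between-arm primary comparison is assigned to an unadjusted single-visit t-test while a mixed model of change is planned alongside it without a stated role; one baseline- and stratum-adjusted longitudinal model should be named as primary

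*Protocol article*

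**What the plan says.** Section 2.10 (Statistical analysis plan) gives the between-arm comparison to a Student t-test: that "test will be used to compare the differences in means between the intervention and the control group for the primary and secondary outcome measures". It names no covariate. The same section states "An intention-to-treat analysis will be employed" and "Linear mixed models will be used to determine changes from baseline among the different study outcomes, with participant number retained as random effect". It also plans a description of dropout: "Estimates of the different sources of attrition bias will be conducted using two-way analysis of variance (ANOVA) models". It does not rank the t-test and the mixed model.

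Section 2.7 (Outcomes) defines the primary outcomes as the "difference in weight, BMI, waist circumference, and body fat percentage between the arms after both the active and inactive phases"; the Abstract is similar. Section 2.8 (Randomization and allocation) states "All participants will be stratified by BMI using the World Health Organization (WHO) cutoff", with one stratum for BMI 25–30 and one above 30 kg/m². Table 2 in section 2.9 shows all four primary outcomes measured at month 0 and at months 3, 6, 9 and 12. Section 2.5 (Sample size calculation) is framed on 5% weight loss after 6 months, and the Introduction sets the aim as 5–10% weight loss, with reductions in the other three measures.

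**The concern.** The design collects what a precise comparison needs: a baseline for each outcome, four follow-up visits and a stratification factor closely tied to the outcomes. The one test assigned to the primary between-arm question uses none of it. There are three consequences.

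- **Scale is not fixed.** Sections 2.7 and 2.10 do not say whether end-of-phase values or changes are compared. Body weight usually varies much more between people than it changes within a person over six months, so this choice can decide whether the trial has reasonable power.
- **Missed visits.** A t-test at month 6 or 12 can use only people measured then (and, if on change, also at baseline). Their data from other visits do not contribute. Dropout related to poor weight loss could bias the comparison.
- **Two unranked analyses.** The t-test and the mixed model can disagree at the same significance level. If the choice between them is made after the data are seen, it is open to the result.

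**Working it through.** **Inputs from the documents.** 26 per arm before dropout, 62 recruited, 20% dropout, 80% power and a target of 5% weight loss (section 2.5); two-sided alpha 0.05 (section 2.10).

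**Inputs assumed, because the documents do not give them.** Mean weight 75–85 kg, so 5% is 3.75–4.25 kg; SD of weight 10–16 kg; baseline-to-follow-up correlation ρ from 0.7 to 0.95, with equal variance at both times.

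**Step 1: the plan's own figure.** Section 2.5 reaches 26 per arm "assuming 80% power, an alpha of 5%, and a 0.25 SD in the main outcome variable".
- Taken literally as 0.05/0.25, the standardised difference is d = 0.2, which needs 393 per arm. The stated 26 is not reproduced.
- An unstated d = 0.8 does give 26 per arm by the t-test, with power 80.7%. For a 5-point difference, 26 per arm at 80% power implies an SD of 5/0.792 = 6.3 percentage points. That is plausible only as an SD of percent change; at 75 kg it is about 4.7 kg.
- The sample size is a separate matter. It is used here only to give a change SD consistent with the stated 26.

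**Step 2: t-test on raw end-of-phase weight.** d = (5% of the mean)/SD, with power from the noncentral t distribution on 50 degrees of freedom.
- Mean 80 kg, SD 12 kg: d = 4/12 = 0.333, power 22%.
- Mean 75 kg, SD 15 kg: d = 3.75/15 = 0.25, power 14%.
- Mean 85 kg, SD 10 kg: d = 4.25/10 = 0.425, power 32%.
- Alternative set-up: mean 75 kg, change SD 4.7 kg independent of baseline. The follow-up SD is √(baseline SD² + 4.7²). Simulated power is 22%, 16% and 12% for baseline SD 10, 13 and 16 kg. For 16 kg, √(256 + 22.1) = 16.7 and d = 3.75/16.7 = 0.225.

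Together the range is about 12–32%.

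**Step 3: the same data with baseline adjustment.** Residual variance is (1 − ρ²) times the raw variance.
- Mean 80 kg, SD 12 kg: at ρ = 0.9, d = 0.333/√0.19 = 0.765 and power is 77%. At ρ = 0.8 it is 50%, and at ρ = 0.95 it is 97%.
- Alternative set-up: about 79% for all three baseline SDs.
- Over means 75–85 kg, SD 10–15 kg and ρ 0.8–0.95, adjusted power runs from 31% to 99.8%, so 77–79% describes the central cases only.

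**Step 4: t-test on change from baseline.** With the d = 0.8 that 26 per arm implies, power is 80.7%. Adjustment multiplies the variance by (1 + ρ)/2:
- ρ = 0.7: d = 0.8/√0.85 = 0.868, power 87%.
- ρ = 0.8: 85%.
- ρ = 0.9: 83%.
- ρ = 0.95: 82%.

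The gain is about 1–6 points. In the alternative set-up, where change is independent of baseline, d = 3.75/4.7 = 0.798, and the unadjusted t-test on change already has about 80%, so adjustment adds nothing.

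**Step 5: missed visits.** 20% of 62 is 12.4, so about 12 randomised people could be absent from a month-6 or month-12 t-test. Those seen at an earlier follow-up visit would contribute to a longitudinal model.

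**The case against.** The strongest reply is that an unadjusted t-test between randomised arms is valid, and that the plan as a whole does not neglect its data: section 2.10 also has a mixed model of change, which uses baseline and partly observed participants, and an analysis of attrition. Covariate lists and missing-data rules are commonly left to a full analysis plan, which is not shown. The trial is also labelled a pilot.

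Much of this stands, and it rules out several stronger readings that a reader might infer.

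- **That the t-test wastes most of the power.** This needs the raw-value reading. Section 2.7 and the Abstract permit it, but section 2.10 does not state it, and section 2.5 and the Introduction point to change. On change, step 4 shows little or no loss.
- **That everyone with a missed visit is discarded.** A t-test at one visit drops only those missing that visit, or missing baseline if it is on change.
- **That the protocol contradicts its intention-to-treat statement.** No available-case rule is written. The tension follows from how a single-visit t-test works, and the lack of a stated missing-data method is not itself a fault of an article.
- **That chance baseline imbalance rivals the target effect.** The standard error SD × √(2/26) is 2.8–4.4 kg for SD 10–16 kg, against 3.75 kg. It assumes simple randomisation, and blocked stratification by BMI should limit imbalance in weight.

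What the reply does not remove is that section 2.10 does make a choice: the only method expressly assigned to the between-arm primary comparison is the t-test. The mixed model, as described, is for change from baseline and names only a participant random effect. A better assignment of roles is available at no cost.

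**Conclusion.** The point holds as a should-fix, free improvement. The between-arm primary inference is given to a test that leaves out the baseline value, the BMI stratum and anyone unmeasured at the visit concerned, and its relation to the mixed model is not settled. These features hold whichever scale is used.

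The size does depend on scale. It is severe if raw end-of-phase values are tested (about 12–32% power against 77–79% adjusted in the central cases) and small if changes are tested (about 80%, with 1–6 points to gain for ρ 0.7–0.95). All of these figures rest on an assumed weight mean, SD and correlation, and on the effect size that 26 per arm implies. The benefit of the stratum term was not quantified. The documents do not show that the trial will be analysed on the unfavourable scale, only that they leave it open.

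**What to change.** Replace the t-test sentence in section 2.10 with one primary analysis: a longitudinal linear mixed model of change from baseline (percent change for weight), with arm, visit, arm-by-visit interaction, baseline value and BMI stratum as fixed effects, and participant as the random effect already planned. Include every randomised participant with any post-baseline value, in the assigned arm. Report the between-arm differences at months 6 and 12 with 95% confidence intervals, matching the ends of the active and inactive phases. Keep the t-tests as descriptive support, and say in section 2.7 that the primary outcomes are changes from baseline.

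Participants with no post-baseline value still contribute nothing to this model, so their number should be reported by arm.

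The cost is wording only: no new data, visits or participants. The change should be made before anyone sees outcome data by arm.
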